##### Meibomian Gland Test

The meibomian gland test will be used to evaluate meibomian gland function in terms of quality and expressibility. In the normal eyelid, the meibum is clear and expressed readily under gentle pressure. However, the meibum becomes opaque and difficult to express in patients with meibomian gland dysfunction [43].

To evaluate the expressibility of meibum, five meibomian glands in the central area of the upper or lower eyelids will be assessed under a slit-lamp microscope after applying firm digital pressure. Patients will be scored from 0 to 3 based on the following criteria: 0, all glands expressible; 1, 3–4 glands expressible; 2, 1–2 glands expressible; and 3, no glands expressible. Meibum quality will be evaluated by observing eight central meibomian glands of the upper and lower eyelids and scored from 0 to 3: 0, clear; 1, cloudy; 2, cloudy and particulate; and 3, opaque toothpaste-like meibum [44]. Both meibum quality and expressibility will be assessed at weeks 0, 6, 12, and 14.

##### Visual Analog Scale (VAS)

The 100 mm visual analog scale (VAS) is a patient-reported outcome that evaluates ocular discomfort, such as ocular pain, itching, dryness, burning, or foreign body sensation. Participants will be scored according to ocular discomfort severity on a 100 mm line, with higher scores representing more severe symptoms. This will be assessed at weeks 0, 6, 12, and 14.

##### Standard Patient Evaluation for Eye Dryness-II (SPEED-II)

The Standard Patient Evaluation for Eye Dryness-II (SPEED-II) is a questionnaire developed to track the progress of dry eye symptoms over time [45]. It is a valid and reliable questionnaire that assesses the severity and frequency of dry eye symptoms, including irritation, dryness, scratchiness, grittiness, burning, soreness, watering, and eye fatigue. The total score ranges from 0 to 28, and dry eye symptoms can be graded as mild (0–4), moderate (5–8), or severe (>8). It monitors three different timeframes: now, within the last 72 h, and within the last 3 months [46]. In this trial, SPEED-II will be measured at weeks 0, 6, 12, and 14.

Compared with the OSDI, SPEED-II includes questions related to the severity of dry eye symptoms, and the symptoms listed in OSDI and SPEED-II are not identical. SPEED-II has a timeframe of 3 months, while OSDI covers 1 week prior to the evaluation [47]. Recently, the use of SPEED-II has increased since the sensitivity and specificity are reported to be 0.90 and 0.80, respectively [48].

#### 2.6.3. Exploratory Efficacy Outcomes

##### Biomarkers (IFN-γ, IL-1β, TNF-α, and MMP-9)

Biomarkers of interferon-gamma (IFN-γ), interleukin-1beta (IL-1β), tumor necrosis factor-α (TNF-α), and matrix metalloproteinase-9 (MMP-9) will be measured to investigate the inflammatory effect of USL on patients with DED. Recent studies have reported that proinflammatory cytokines TNF-α and IL-1β, and anti-inflammatory cytokine IFN-γ play important roles in ameliorating DED. Moreover, IL-1β, IFN-γ, and TNF-α are the most important cytokines used for DED treatment in animal models [49]. MMP-9 is also considered as valuable therapeutic target in DED by playing a vital role in the pathogenesis of corneal disease. Recent clinical and animal studies also introduce MMP-9 as a biomarker of ocular surface inflammation in DED [50]. IFN-γ, IL-1β, and TNF-α will be obtained from each of the subject’s serum and will be analyzed by a designated laboratory, and MMP-9 activity will be measured from tears (InflammaDry; Rapid Pathogen Screening, Inc., Sarasota, FL, USA). It will be evaluated before and after administration of the trial medication (weeks 0 and 12).

#### 2.6.4. Safety Outcomes

Adverse events (AEs), vital signs, laboratory examinations, visual acuity, and IOP will be assessed throughout the trial to evaluate safety. At every visit, AEs, vital signs, visual acuity, and IOP will be observed, and laboratory tests will be performed before and after taking the trial medication. We will record every unexpected symptom or sign during the trial by asking the participants questions and through the investigator’s examination. However, if serious AEs occur during the trial, the patient will be immediately removed from the trial and proper treatment will be provided. Visual acuity and IOP will be examined as recommended by the Ministry of Food and Drug Safety in Korea for clinical trials on ocular diseases. The laboratory tests will include liver function, routine blood, and urine tests.

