
#### 2.2.3. Sample Size

The estimated sample size required for this trial is 120 patients (40 patients per group), based on previous comparable studies [34,35,36]. Although we could not calculate the sample size based on the exact effect size, as our study is the first trial using USL on patients with DED, we calculated the sample size based on previous studies expected to have similar effects. We assumed the difference in the changes in TBUT as 1.3, and the standard deviation (SD) as 1.8 from baseline to post-intervention between the control and standard-dose USL groups. The power to detect differences is assumed to be 0.8, with the two-sided significance level set at 0.05. The ratio of the allocation of subjects between groups is 1:1:1, and the dropout rate is assumed to be 0.2.

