### 2.4. Blinding

All participants and investigators, including outcome assessors, will be blinded throughout the trial. The trial medication was packaged identically with a placebo developed to have the same color, taste, and smell as the USL intervention medicine. The subject identification code will be sealed in an opaque envelope, stored in a locked cabinet, and not disclosed until the end of the trial, except if a serious adverse reaction occurs.

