##### Tear Break-Up Time (TBUT)

TBUT was chosen as the primary outcome for objective signs in our study because TBUT assesses tear film stability, which is one of the essential diagnostic criteria for diagnosing tear film abnormalities and DED [37]. TBUT is also one of the most frequently used diagnostic tests in clinical practice for DED [38].

The procedure follows a standardized methodology. For the TBUT test, subjects will be instructed to sit at the slit-lamp microscope with their chin on the chin rest. Sodium fluorescein will then be applied to both eyes on the inferior temporal bulbar conjunctiva. Each participant will be instructed to blink naturally three times to distribute fluorescein on the ocular surface. Then, the participants will be asked to cease blinking until instructed otherwise. The time between eye opening and the first appearance of a dry spot in the tear film will be measured in seconds using a slit-lamp microscope (BQ-900; Haag-Streit, Bern, Switzerland). The cut-off value of TBUT for the diagnosis of DED is reported to be less than 10 s for an abnormal tear film, between 5 s and 10 s for a marginal tear film, and less than 5 s for severe DED [39]. With reference to this, participants with a TBUT ≤ 10 s will be included in this trial. The TBUT for each participant will be measured at screening, week 6, week 12, and week 14, and we will measure the changes in mean TBUT from screening to week 12 between the intervention and control groups as the primary outcome.

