##### Ocular Surface Disease Index (OSDI)

The OSDI is the primary outcome measure of subjective symptoms in this trial. It is the most commonly used questionnaire for patients with DED in clinical trials. The OSDI has been validated to measure the severity of DED, and it comprises psychometric symptoms related to DED [40]. Owing to its strong establishment in DED, a consensus to use the OSDI was reached by a related committee [15].

The OSDI measures the frequency of symptoms, environmental triggers, and vision-related quality of life within 1 week. It comprises 12 questions, each of which is graded on a scale of 0–4, where 0 indicates none of the time, 1 as some of the time, 2 as half of the time, 3 as most of the time, and 4 as all of the time [40]. The total OSDI score is calculated as follows: OSDI = [(sum of scores for all questions answered) × 100]/[(total number of questions answered) × 4]

Thus, the OSDI score ranges from 0 to 100; the higher the score, the worse the quality of life. According to OSDI scores, patients can be categorized as having normal (0 to 12 points), mild (13 to 22 points), moderate (23 to 32 points), or severe (33 to 100 points) ocular surface disease. In our trial, patients with OSDI scores ≥ 23 points will be included, meaning that those who have moderate-to-severe symptoms will all be included. The OSDI score will be measured at screening, week 6, week 12, and week 14, and the changes in OSDI from screening to week 12 will be the primary outcome of this trial.

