### 2.7. Statistical Analysis

Statistical analyses of all outcomes will be conducted by an independent statistician using SAS Version 9.4 Analytics Pro software. Continuous variables will be presented as the mean ± SD and categorical variables will be presented as frequencies and percentages. For efficacy analysis, a full analysis set (FAS) based on intention-to-treat (ITT) analysis will be performed as the primary analysis, and PP analysis will be used for secondary analysis. All randomized participants who are evaluated at least once after administration of the trial medication will be included in the FAS, and only those who complete the trial without violating the protocol will be included in the PP set. A safety analysis will be conducted for all participants who are randomized and administered the trial medication at least once.

The primary and secondary efficacy outcomes will be analyzed using the mixed-effects model for repeated measures, with each group and visit set as fixed effects and participants as random effects. In addition, the difference between pre- and post-treatment within groups will be analyzed using Student’s paired *t*-test or Wilcoxon signed-range test, depending on normality. A multiple imputation method will be used for missing values. The efficacy of USL will be accepted at a significance level of 2.5% in both TBUT and OSDI compared with the placebo, whereas other secondary outcomes will be accepted at a 5% significance level.

To analyze safety outcomes, Fisher’s exact test will be used to compare the number of AEs between the groups, and Student’s paired *t*-test or the Wilcoxon signed-rank test will be performed to analyze the differences between pre- and post-treatment laboratory variables, vital signs, visual acuity, and IOP. Demographic characteristics will be analyzed using the Wilcoxon rank-sum test or independent *t*-test for continuous variables and Fisher’s exact test or the chi-square test for categorical variables.

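### As written, any serious AE ends trial participation, so the remaining scheduled safety assessments, and before week 12 the primary measurements, may be lost

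*Protocol article*

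**What the plan says.** Section 2.6.4 (Safety Outcomes) states that "if serious AEs occur during the trial, the patient will be immediately removed from the trial" and that suitable treatment will be given. It sets no condition on causality and leaves no discretion to the investigator. It speaks of leaving the trial, not of stopping the tablets. No other section of the article provides for visits after such a removal.

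The assessments at stake are these:

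- **Safety.** Section 2.6.4: "At every visit, AEs, vital signs, visual acuity, and IOP will be observed". Table 1 schedules laboratory tests at screening and week 12 only.
- **TBUT.** Section 2.6.1: "we will measure the changes in mean TBUT from screening to week 12 between the intervention and control groups as the primary outcome".
- **OSDI.** Section 2.6.1: "the changes in OSDI from screening to week 12 will be the primary outcome of this trial".
- **Analysis sets.** Section 2.7: "a full analysis set (FAS) based on intention-to-treat (ITT) analysis will be performed as the primary analysis". On entry to that set: "All randomized participants who are evaluated at least once after administration of the trial medication will be included in the FAS". The safety analysis takes every randomized participant who was dosed at least once.
- **Blinding.** Section 2.4: the code is "not disclosed until the end of the trial, except if a serious adverse reaction occurs".
- **Planned loss.** Section 2.2.3: "the dropout rate is assumed to be 0.2".

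**The concern.** Stopping a study drug and leaving a study are different decisions. A serious AE often justifies the first. It seldom requires the second, unless the participant withdraws consent. Read plainly, section 2.6.4 makes them one decision.

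The first thing at stake is safety information. The Discussion calls this the first clinical trial of USL for DED. The people whose later vital signs, visual acuity, IOP and laboratory values matter most are those who have had a serious event, and the rule takes them out of the schedule. Section 2.7 compares laboratory variables, vital signs, visual acuity and IOP before and after treatment with paired tests. A participant removed before week 12 has no scheduled post-dose laboratory value to pair.

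The second is the missing-data mechanism. Removal before week 12 makes both primary outcomes missing by rule, for a reason that may be related to treatment. Multiple imputation would then stand in for values that could have been measured. That fits poorly with an analysis described as based on ITT.

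**Working it through.** **1. What is lost, by time of event.** The scheduled visits after the baseline visit are weeks 6, 12 and 14 (Table 1).

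| Serious AE occurs | Scheduled visits lost | Week 12 TBUT, OSDI and laboratory test | FAS |
|---|---|---|---|
| Before week 6 | 3 | lost | may be outside, unless evaluated at an unscheduled visit |
| Weeks 6 to 12 | 2 | lost | in |
| Weeks 12 to 14 | 1 | kept | in |

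**2. The plan's own sample size.** Inputs from section 2.2.3: difference 1.3, SD 1.8, two-sided alpha 0.05, power 0.8, dropout 0.2. The two-sample t-test needs 31.09, rounded up to 32 per group. Then 32/(1 − 0.2) = 40 per group, or 120 in total. The stated figure reproduces. The dropout allowance is 40 × 0.2 = 8 per group.

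**3. Participants removed.** The article gives no serious AE rate, so 1-5% is assumed.
- Whole trial: 120 × 0.01 = 1.2 to 120 × 0.05 = 6.
- Per group: 0.4 to 2.

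The broad comorbidity exclusions in section 2.2.2 point to the low end.

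**4. Visits lost.** Events are assumed to be spread evenly over 14 weeks.
- Per removed participant: (3 × 6 + 2 × 6 + 1 × 2)/14 = 2.29.
- Whole trial: 1.2 × 2.29 = 2.7 to 6 × 2.29 = 13.7.

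**5. Participants without week 12.** The share of events before week 12 is 12/14.
- Per group: 0.4 × 12/14 = 0.34 to 2 × 12/14 = 1.71.
- Against the dropout allowance: 0.34/8 = 4% to 1.71/8 = 21%.

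**6. Effect on the TBUT comparison.** This takes the unfavourable case, in which all these losses come on top of the 20% dropout. SE = 1.8 × √(2/n); power is from the noncentral t distribution.

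| Evaluable per group | SE (s) | Power, alpha 0.05 | Power, alpha 0.025 |
|---|---|---|---|
| 32 | 0.45 | 0.812 | 0.72 |
| 31.66 (1% rate) | 0.45 | 0.807 | 0.72 |
| 30.29 (5% rate) | 0.46 | 0.789 | 0.69 |

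The last column uses the 2.5% level that section 2.7 sets for TBUT and OSDI. The starting power is lower there, but the fall due to removals is about the same: 0.02 to 0.03 at most.

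**The case against.** The strongest reply is that the article condenses a fuller protocol. Withdrawal procedures, an exit examination and follow-up of the event are the kind of detail an article leaves out. Section 2.6.4 promises treatment, and section 2.8 commits the trial to Good Clinical Practice and to proper reporting of AEs. Its wording on laboratory tests, before and after taking the medication, is compatible with a draw at removal. Section 2.7 does not say that the evaluation needed for the FAS must come from a scheduled visit.

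Much of this stands. A reader might infer that all follow-up certainly stops at the event. The article does not say so; it says that the participant leaves the trial. The losses are therefore conditional on what the full protocol adds. A reader might also infer that the serious AE itself goes uncounted. It does not, because the safety set keeps everyone who was dosed. Nor are all three later visits always lost; that holds only for events before week 6.

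The reply does not remove the point. The criticism is of a rule that the article states, not of missing detail. An exit visit at the time of the event would not supply a week 12 measurement.

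A second reply is that the 20% dropout allowance, the mixed model and multiple imputation already cover the losses. They cover the numbers. They do not fully cure missingness that arises because of the event.

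A third is that measurements taken off medication, and possibly after unblinding, are open to bias, so that keeping them is partly a matter of preference in a dose-finding trial. That is fair for OSDI and TBUT, although the ITT label favours collecting them. It has little force for the safety assessments.

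**Conclusion.** The concern holds as a should-fix point about a stated rule. As written, section 2.6.4 ties leaving the trial to any serious AE. Unless the full protocol provides otherwise, scheduled safety follow-up is lost, and for events before week 12 so are the primary time point and the only scheduled post-dose laboratory test.

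The number is small. At the assumed 1-5% rate with even timing, about 1 to 6 of 120 participants are removed, 3 to 14 scheduled visits are lost in the whole trial, and 0.3 to 1.7 participants per group lack week 12. A reader might infer that the efficacy result is in danger, but the figures do not support that. Power at the planned 5% level falls at most from 0.81 to 0.79, the SE moves from 0.45 to 0.46 s, and the losses may well sit within the dropout allowance. No bias of any particular size in the TBUT estimate has been shown.

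The case rests on safety follow-up of the participants in whom it matters most, and on avoidable event-related missing data under an ITT label. Confidence is medium, because the event rate and timing are assumed and the full protocol is not at hand.

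**What to change.** Reword the sentence in section 2.6.4 along these lines: after a serious AE, study medication is stopped as clinically needed and appropriate treatment is given; the event is followed to resolution or stabilisation; the participant remains in the trial for the remaining scheduled safety and efficacy assessments, including the week 12 laboratory tests, TBUT and OSDI, unless consent is withdrawn.

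Because section 2.4 allows disclosure of the code after a serious adverse reaction, add a case report form field for whether and on what date the code was broken. A sensitivity analysis leaving out efficacy data collected after unblinding is optional. With roughly 0 to 2 participants per group it would tell little.

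The cost is one reworded sentence and one form field. The remaining visits are already in the schedule, so the change adds no new visit type apart from whatever contact is needed to follow the event. The downside is that about 3 to 14 visits in the whole trial (same assumptions) would be attended off medication where the drug has been stopped. Some of these participants may be unblinded, which leaves their OSDI and TBUT open to bias, and some may decline to attend.

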### 2.7. Statistical Analysis

Statistical analyses of all outcomes will be conducted by an independent statistician using SAS Version 9.4 Analytics Pro software. Continuous variables will be presented as the mean ± SD and categorical variables will be presented as frequencies and percentages. For efficacy analysis, a full analysis set (FAS) based on intention-to-treat (ITT) analysis will be performed as the primary analysis, and PP analysis will be used for secondary analysis. All randomized participants who are evaluated at least once after administration of the trial medication will be included in the FAS, and only those who complete the trial without violating the protocol will be included in the PP set. A safety analysis will be conducted for all participants who are randomized and administered the trial medication at least once.

The primary and secondary efficacy outcomes will be analyzed using the mixed-effects model for repeated measures, with each group and visit set as fixed effects and participants as random effects. In addition, the difference between pre- and post-treatment within groups will be analyzed using Student’s paired *t*-test or Wilcoxon signed-range test, depending on normality. A multiple imputation method will be used for missing values. The efficacy of USL will be accepted at a significance level of 2.5% in both TBUT and OSDI compared with the placebo, whereas other secondary outcomes will be accepted at a 5% significance level.

To analyze safety outcomes, Fisher’s exact test will be used to compare the number of AEs between the groups, and Student’s paired *t*-test or the Wilcoxon signed-rank test will be performed to analyze the differences between pre- and post-treatment laboratory variables, vital signs, visual acuity, and IOP. Demographic characteristics will be analyzed using the Wilcoxon rank-sum test or independent *t*-test for continuous variables and Fisher’s exact test or the chi-square test for categorical variables.

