### 2.2. Participants

#### 2.2.1. Inclusion Criteria

Participants who meet the following criteria will be enrolled in this trial: (1) subjects aged over 19 years; (2) subjects with dry eye symptoms (stiffness, foreign body sensation, irritation, bloodshot eyes, itching, blurred vision, pain, etc.) for at least 3 months; (3) subjects who have had both eyes screened, with a corrected visual acuity of 0.2 or more; (4) subjects with a fluorescein corneal staining score (Oxford grading) ≥ 2, tear break-up time (TBUT) ≤ 10, and Schirmer’s test ≤ 10 mm at screening; (5) subjects with an Ocular Surface Disease Index (OSDI) ≥ 23 at screening; and (6) subjects who voluntarily agree and provide written informed consent to participate in the clinical trial.

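### The repeated-measures model in section 2.7 lists no pre-treatment covariate, so the screening TBUT and OSDI values go unused for precision; the gain from adding them is real but cannot be fixed from the document

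*Protocol article*

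**What the plan says.** Section 2.7 (Statistical Analysis) gives one model for the primary and secondary efficacy outcomes: a mixed-effects model for repeated measures, "with each group and visit set as fixed effects and participants as random effects". No screening or baseline value is named among its terms, there or elsewhere in the article.

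Both primary outcomes are defined as changes from screening. For TBUT, "we will measure the changes in mean TBUT from screening to week 12 between the intervention and control groups as the primary outcome"; for OSDI, "the changes in OSDI from screening to week 12 will be the primary outcome of this trial". Both are scheduled before treatment: "The TBUT for each participant will be measured at screening, week 6, week 12, and week 14" and "The OSDI score will be measured at screening, week 6, week 12, and week 14". Table 1 shows neither repeated at week 0, so the screening value is the only pre-treatment value for these two outcomes.

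Both screening values are also entry criteria in section 2.2.1: "tear break-up time (TBUT) ≤ 10, and Schirmer’s test ≤ 10 mm at screening" and "subjects with an Ocular Surface Disease Index (OSDI) ≥ 23 at screening".

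Section 2.2.3 supplies the only variance figure: "We assumed the difference in the changes in TBUT as 1.3, and the standard deviation (SD) as 1.8". No SD at a single time point, no correlation between screening and week 12, and no variance of any kind for OSDI is given.

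**The concern.** An unadjusted change score fixes the coefficient on the screening value at 1. If the true within-arm regression of the week 12 value on the screening value has a slope other than 1, part of the variance of the change can be predicted from screening, and the listed model leaves that part in the error. The random participant effect does not recover it:

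- If the response is the change score, the dependence of change on screening stays in the error.
- If screening is entered as one of the visits and the arms may differ there, the week 12 contrast is again the unadjusted change.
- If the response is the raw week 12 value, the variance given up is rho² (25% to 49% at rho 0.5 to 0.7), which is at least as large as for a change score with equal SDs.

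What is at stake is the width of the confidence interval and the power for two primary outcomes with 40 participants planned per arm.

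**Working it through.** **1. Reproduce the planned size.** Inputs from section 2.2.3: difference 1.3, SD of change 1.8, power 0.80, two-sided 5%, dropout 0.2. The two-sample t calculation gives 32 per arm; 32 / (1 − 0.2) = 40 per arm, 120 in total, as stated. The normal approximation gives 31, then 39 per arm. The 32 completers are used below.

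**2. Unadjusted TBUT power with 32 per arm (noncentral t).** 81% at two-sided 5% and 72% at two-sided 2.5%. The 2.5% is the level in section 2.7, which does not state sidedness; two-sided is assumed here.

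**3. Formula for the saving.** Let rho be the within-arm correlation between screening and week 12, and k the screening SD divided by the week 12 SD. In units of the week 12 variance:

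- variance of the change: k² + 1 − 2·rho·k
- variance after adjustment: 1 − rho²
- saving: 1 − (1 − rho²)/(k² + 1 − 2·rho·k) = (k − rho)²/(k² + 1 − 2·rho·k)

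With k = 1 this is (1 − rho)/2. It is zero when k = rho, that is, when the regression slope rho/k equals 1. Both rho and k are assumptions.

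**4. Equal SDs (k = 1).** Effective SD = 1.8 × √(1 − saving); power at two-sided 2.5%.

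| rho | saving | effective SD | TBUT power |
|---|---|---|---|
| 0.5 | 25% | 1.559 | 85% |
| 0.6 | 20% | 1.610 | 82% |
| 0.7 | 15% | 1.660 | 80% |
| 0.8 | 10% | 1.708 | 77% |
| 0.9 | 5% | 1.754 | 75% |

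**5. Smaller screening SD because entry is restricted.** Two ways to express this:

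*(a) Fix rho in the trial population and lower k.*

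| k | saving at rho 0.5 / 0.6 / 0.7 | power |
|---|---|---|
| 0.9 | 17.6% / 12.3% / 7.3% | 81% / 78% / 76% |
| 0.8 | 10.7% / 5.9% / 1.9% | 77% / 75% / 73% |
| 0.7 | 5.1% / 1.5% / 0% | 75% / 73% / 72% |

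*(b) Hold the slope fixed and shrink the screening variance.* Selecting on the screening value leaves a linear slope unchanged. If the unrestricted SDs are equal, the slope is the unrestricted rho. With a fraction f of the screening variance remaining, the saving is (1 − rho)f / [(1 − rho)f + 1 + rho].

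- f = 0.75: 0.375/1.875 = 20% at rho 0.5; 0.225/1.925 = 12% at rho 0.7; power 82% and 78%.
- f = 0.5: 0.25/1.75 = 14% at rho 0.5; 0.15/1.85 = 8% at rho 0.7; power 79% and 76%.

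**6. OSDI.** No difference, SD or correlation is given, so there is nothing to compute.

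**The case against.** The strongest reply is that this is a condensed article. The model occupies one sentence, which also leaves out the group-by-visit term, the covariance structure and the exact response. An analysis plan not shown may add the covariate. A repeated-measures model that includes screening as a visit and constrains the arms to a common screening mean would reach about the same precision. This stands as a limit on certainty. It does not remove the point: the article names its fixed effects, the screening value is not among them, and the model followed as written is less precise.

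Several stronger readings are tempting but unsupported:

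- *That a definite 15% to 25% of the variance is lost.* This needs both rho of 0.7 to 0.5 and equal SDs, and neither is documented.
- *That the entry cut-offs strengthen the case by pulling the slope below 1.* They work the other way: selection on the screening value leaves a linear slope alone and shrinks the screening variance, and with it the saving.
- *That the unadjusted result would be biased or invalid.* Randomisation keeps it unbiased with type I error controlled, and chance imbalance at screening is already reflected in its standard error.
- *That adjustment rescues an underpowered trial on both primary outcomes.* The shortfall comes from sizing at 5% in section 2.2.3 and testing at 2.5% in section 2.7, which is a separate matter. If the 2.5% is one-sided, it equals the two-sided 5% and unadjusted TBUT power is 81%. For OSDI no power can be stated.

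**Conclusion.** The point holds as one of efficiency. The listed model leaves out a covariate the trial already collects, and the cost is precision, not validity. For TBUT, the variance saving is 25% to 5% for rho 0.5 to 0.9 with equal SDs, and from close to 0% up to about 20% in the restricted-entry scenarios examined. Power at two-sided 2.5% with 32 completers per arm therefore moves from 72% to somewhere between about 72% and 85%. The upper end needs rho 0.5 and equal SDs; the lower end needs a slope at or near 1. A correlation below 0.5 with equal SDs would save more (35% at rho 0.3). In large samples adjustment is never less efficient, so the direction is secure even though the size is not.

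**What to change.** In section 2.7, before unblinding, add the pre-treatment value of the same outcome and its interaction with visit as fixed covariates in the repeated-measures model. Following Table 1, this is the screening value for TBUT, OSDI and corneal staining, and the week 0 value for the other continuous secondary outcomes. If the analysis plan already contains these terms, the published model should say so.

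The cost is one sentence, about a degree of freedom per term, and no new data or visits. Prespecifying it also removes a later choice between adjusted and unadjusted results. Any expected gain should be quoted with its assumed rho and SD ratio, and the 5% and 2.5% significance levels still need to be reconciled separately.
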